## Discussion

3

This study presets the protocol of a prospective, single-center, cohort study which aims to investigate the impact of inflammatory-mediated myocardial fibrosis on the risk of recurrence after successful catheter ablation of AF.

Although AF ablation procedures are constantly improving, recurrences continue to be problematic as a significant proportion of patients present with AF relapse despite an optimum management in the post-ablation period.^[1,4]^ In the latest years, a large number of studies tried to identify predictors for a successful outcome on long term after AF ablation, however reliable clinical markers to predict sinus rhythm maintenance or AF recurrence have not been identified so far. The main contribution of the present study will be to validate new clinical features, such as inflammatory biomarkers, epicardial fat, ventricular remodeling or myocardial fibrosis, as predictors of AF recurrence in patients who are scheduled for catheter ablation. In this trial we hypothesize that several imaging markers associated with cardiac structural alteration, provided by CMR (such as LA, LV fibrosis, atrial volumes or the amount of epicardial fat), associated with serum inflammatory biomarkers (IL-6, MMP-9, hsCRP) could form a powerful prediction panel to predict the risk of AF recurrence in the post ablation period, reflecting the impact of inflammatory-mediated myocardial fibrosis on the risk of arrhythmia.

The relationship between inflammation, myocardial injury and atrial fibrillation has been extensively studied in the recent years.^[5]^ It is well known that a higher amount of atrial fibrotic tissue can favor atrial arrhythmogenesis.^[2,6]^ At the same time, the amount of contrast enhancement in the LA wall, considered to represent the volume of fibrotic tissue of the total LA wall, has been recently described by prospective trials to be independently associated with the likelihood of recurrent arrhythmia after ablation.^[2,6,7]^ Previous studies showed that pre-existing fibrosis on LGE-CMR was the strongest independent predictor of ablation procedure failure and arrhythmia recurrence.^[8]^ McGann et al proved that subjects with >30% atrial fibrosis on LGE images at baseline had a 71% chance of AF recurrence at 1 year.^[9]^

Beside baseline evaluation, several studies suggest that quantification of post ablation LA scarring may play a role in determination of the AF recurrence risk.^[10]^ Several recent studies managed to assess the feasibility of LGE-MRI in detecting both pre-existing and post-ablation atrial and ventricular fibrosis.^[8,11–14]^ Their results raised interest in the use of CMR as a periprocedural risk assessment tool. Despite these promising results, the assessment of atrial and ventricular fibrosis has not yet been widely adopted in clinical practice.^[15–18]^ We should not forget that the capacity of LGE-CMR to detect fibrosis in the atria is still controversial due to the lack of reproducibility. Thus, this trial aims to validate myocardial fibrosis, targeting both atrial and ventricular fibrosis quantified by CMR, as predictor for AF recurrence.

Previous observational studies showed that elevation of several inflammatory serum biomarkers, such as hsCRP or IL-6, are associated with occurrence and recurrence of AF, since patients with AF present significantly higher levels of inflammatory biomarkers as compared with subjects maintaining sinus rhythm.^[3,19–22]^ Therefore, the role of inflammation in AF recurrence has been recently proposed as a new and challenging hypothesis to explain the high rate of recurrence after AF conversion.^[3,21,23–26]^ As the exact pathways from inflammation to AF are still unclear, it is presumed that inflammatory cytokines may bind to atrial myocytes inducing tissue damage.^[24]^ In line with this hypothesis, the FIBRO-RISK trial aims to investigate the correlation between inflammatory biomarkers and cardiac fibrosis, evaluated via LGE-CMR, in order to prove the impact of inflammatory-related myocardial fibrosis on the risk of recurrence after successful catheter ablation of AF.

Besides inflammation, neurohormonal activation, classically associated with ventricular dysfunction, has been shown to play a significant role in the recurrence of AF following pulmonary vein isolation.^[20,21,23–26]^ A very recent study demonstrated that in patients admitted in an intensive care facility, the presence of ventricular remodeling leading to ventricular dysfunction was associated with a higher incidence of AF and conduction abnormalities.^[27]^ NT-proBNP is a biomarker reflecting ventricular dysfunction, which has been shown to predict AF recurrence unrelated to ablation procedure.^[28,29]^ However, it still remains unclear if these biomarkers are useful predictors of AF recurrence after ablation. In the FIBRO-RISK study, we aim to validate, for the first time in the literature, the role of ventricular remodeling, serum biomarkers associated with ventricular dysfunction, inflammation and myocardial fibrosis, assessed by LGE-CMR, as independent predictors of AF recurrence after successful catheter ablation, in order to prove that inflammation can play a significant role in the complex interrelation between myocardial dysfunction, remodeling and AF recurrence.

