## Abstract

**Introduction::**

Interventional ablation has been demonstrated to represent an effective therapy in patients with atrial fibrillation (AF), leading to restoration and maintenance of sinus rhythm in the majority of cases. However, recurrence of AF is encountered in 35% to 40% of cases, and the causes for this frequent complication have not been elucidated so far.

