### Background and rationale

1.1

Atrial fibrillation (AF) has an increasing prevalence, being currently the most frequent type of supraventricular arrhythmia and representing a significant burden for the healthcare system. In most of the cases, myocardial tissue located at the level of the pulmonary veins represents the origin of AF. The pathophysiology of AF is still incompletely understood, several studies suggesting that profibrotic and inflammatory processes can play a crucial role in the development of AF.^[1]^ So far the success rate of AF ablation is not very high, reaching 70% in patients with paroxysmal AF and 50% in cases with persistent AF. Several risk factors for the occurrence and recurrence of AF have been described in the literature, including left atrial (LA) enlargement, left ventricular (LV) dysfunction, the amount of epicardial fat surrounding cardiac structures, or myocardial fibrosis.^[2]^ However, the relationship between inflammatory-mediated myocardial fibrosis and AF recurrence after radiofrequency catheter ablation has not been elucidated so far.^[3]^

Here we present the study protocol of the FIBRO-RISK trial, a prospective, single-center, cohort study which aims to investigate the impact of inflammatory-mediated myocardial fibrosis on the risk of recurrence after successful catheter ablation of AF.

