### Study groups

2.5

One hundred patients with successful ablation of AF who meet the selection criteria will be divided into 2 groups, namely subjects who develop AF recurrence at 1-year post ablation (group 1) and subjects with no recurrence of AF at 1-year post ablation (group 2).

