### Sample size

2.12

The study will include 100 subjects with AF undergoing successful ablation of pulmonary veins via interventional route. After analysis of follow-up data, patients will be distributed in two groups according to the presence or absence of recurrent episodes of AF during the follow-up.

Sample size calculation was performed using the StatMate 2.0 software. For sample calculation, the proportion of event-free population was estimated at 60%. According to this calculation, a sample size of 50 patients in each subgroup has a 90% power to detect an increase in MACE-free rates proportion of 0.29, with a significance level (alpha) of 0.05 (2-tailed). Therefore, the total sample size was established at 100 patients.

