## Conclusions

4

FIBRO-RISK will be the first CMR-based study that will investigate the impact of inflammation-mediated myocardial fibrosis on the risk of recurrence after successful catheter ablation of AF, aiming to validate inflammatory biomarkers and myocardial fibrosis as predictors for AF recurrence.

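### The prediction-panel and independent-predictor aims cannot be met by the one-marker-at-a-time tests in section 2.13 or validated in the single cohort of 100

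*Protocol article*

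**What the plan says.** **The aims.** The study hypothesis, in section 3 (Discussion) of the protocol article, is that CMR markers together with IL-6, MMP-9 and hsCRP "could form a powerful prediction panel to predict the risk of AF recurrence in the post ablation period". Later in the same section the article says "we aim to validate, for the first time in the literature" the role of ventricular remodelling, serum biomarkers, inflammation and fibrosis as independent predictors of recurrence. Section 4 (Conclusions) describes the study as "aiming to validate inflammatory biomarkers and myocardial fibrosis as predictors for AF recurrence", and the abstract closes in the same terms.

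**The data.** Section 2.5 (Study groups) states: "One hundred patients with successful ablation of AF who meet the selection criteria will be divided into 2 groups", according to recurrence at one year. The design is single-centre (section 2.1). No second cohort and no split of the data is described.

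**The analysis.** Section 2.13 (Statistical analysis) lists the t test, the Mann-Whitney test and the Fisher exact test at the 5% level. No method that combines markers appears.

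**The size.** Section 2.12 (Sample size) rests on a comparison of two proportions: "a sample size of 50 patients in each subgroup has a 90% power to detect an increase in MACE-free rates proportion of 0.29".

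**The concern.** A panel is a rule that combines several markers. An independent predictor is one that still carries information once the others are taken into account. Comparing each marker separately between patients with and without recurrence yields neither.

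The gap matters more here because the article's own theory is that inflammation drives fibrosis, so the markers are expected to be correlated. Suppose fibrosis differs between the groups by *d* standard deviations, and an inflammatory marker has within-group correlation *r* with fibrosis but no link of its own with recurrence. That marker will still differ between the groups by *r* × *d*. A t test can then be significant for both, and nothing in 2.13 would tell them apart.

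Two outcomes are possible at the end of the study. Univariate p-values may be reported as evidence for a panel and for independent predictors. Or a panel may be assembled after the recurrences are known and judged in the patients who produced it, in which case its accuracy will look better than it is.

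**Working it through.** **1. The plan's own figure.** Section 2.12 takes 0.60 event-free against 0.60 + 0.29 = 0.89, two-sided alpha 0.05 and 90% power. With pooled proportion (0.60 + 0.89)/2 = 0.745:

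n per group = (1.960 + 1.282)² × 2 × 0.745 × 0.255 / 0.29² = 47.5, so 48.

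Power at 50 per group is 91.4% by the same formula, or 88.6% with a continuity correction. The stated 50 per group and 90% are reproduced. The calculation concerns a difference between two proportions. It says nothing about how many patients or events a multi-marker model would need.

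**2. Number of recurrences.** The abstract says that "recurrence of AF is encountered in 35% to 40% of cases", which is 35 to 40 in 100 and fits the 60% event-free assumption in 2.12. Section 1.1 gives ablation success as "reaching 70% in patients with paroxysmal AF and 50% in cases with persistent AF". If the remainder recur, that is 30 to 50 in 100, depending on case mix.

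**3. Number of candidate markers.**
- Left atrial and left ventricular fibrosis: 2 (section 3).
- Left and right atrial volume: 2 (section 2.10), or 1 if counted once.
- Epicardial fat around the left atrium, the right atrium and the whole heart: 3 (section 2.3), or 1 if counted once.
- IL-6, MMP-9 and hsCRP: 3 (section 3).

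The broad count is 2 + 2 + 3 + 3 = 10, or 11 with NT-proBNP (also raised in section 3). The narrow count is 2 + 1 + 1 + 3 = 7. With 35 to 40 events, events per marker are 35/11 = 3.2 to 40/10 = 4.0 on the broad counts, and 35/7 = 5.0 to 40/7 = 5.7 on the narrow one.

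**4. Aims beside methods.**

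| Stated aim | What it requires | What 2.13 names |
|---|---|---|
| Combined prediction panel | A model or rule joining markers, and a measure of its accuracy | Two-group tests, one marker at a time |
| Independent predictors | Each marker assessed with the others held fixed | The same |
| Validation of either | Patients not used to build the model, or at least resampling | One cohort of 100 |

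**5. Conditional size of the overfitting.** The article states no panel model, so this step assumes one: all candidates entered in an unpenalised logistic model, with the C-statistic measured in the same 100 patients. Markers are independent standard normal noise, with 2000 simulated studies per setting.

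| Markers | Recurrences | Mean apparent C | Share of studies with C ≥ 0.70 | Mean C in new patients |
|---|---|---|---|---|
| 7 | 35 | 0.653 | 13.7% | 0.50 |
| 7 | 40 | 0.650 | 11.6% | 0.50 |
| 10 | 35 | 0.686 | 36.2% | 0.50 |
| 10 | 40 | 0.681 | 32.8% | 0.50 |
| 11 | 35 | 0.695 | 45.4% | 0.50 |
| 11 | 40 | 0.692 | 42.4% | 0.50 |

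A pairwise correlation of 0.3 between markers changes the mean apparent C by no more than 0.001. With 10 markers and 30 to 50 recurrences the mean apparent C runs from about 0.69 down to 0.68. The excess over the truth is therefore about 0.65 − 0.50 = 0.15 with 7 markers and 0.695 − 0.50 ≈ 0.20 with 11.

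**6. If the hypothesis is partly right.** Assume 38 recurrences, with 2 markers truly shifted by 0.4 standard deviations and the rest noise. With 10 candidates the apparent C is about 0.73, against 0.60 in new patients. With 7 candidates it is 0.71 against 0.61.

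**The case against.** The strongest reply is that the article plans no panel model. The panel is a hypothesis in the Discussion, the objectives in section 1.2 are worded as correlations, and section 2.13 contains no regression, score or selection step. This stands, and it is why the figures in steps 5 and 6 are conditional.

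A reader might infer more: that a panel will be built and declared validated in the same 100 patients, so that even pure noise would look predictive. The documents do not support that, for four reasons.
- No fitting procedure is described.
- In sections 3 and 4 and in the abstract, the verb *validate* attaches to individual markers, not to the panel. For markers that the Discussion says earlier studies have linked to recurrence, testing the association in a fresh cohort is a fair form of confirmation.
- An analysis plan that is not shown may contain optimism correction, so its absence from a condensed article is not a fault in itself.
- A noise panel would look only modestly predictive. It reaches 0.70 in about one study in three with 10 markers and about one in eight with 7. The higher counts also treat overlapping fat regions as separate candidates.

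What the reply does not remove is the mismatch on the page. The article does give an analysis section, and the tests named there cannot produce the joint conclusions that the Discussion promises. If no model is fixed in advance, any panel would have to be devised once outcomes are known, which makes optimism worse. Resampling would correct an accuracy estimate, but it would not replace testing in other patients.

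**Conclusion.** The point holds in a limited form. The stated aims of a prediction panel and of independent predictors have no matching method in section 2.13, no sizing in section 2.12, and no data beyond one cohort of 100 with about 35 to 40 recurrences (30 to 50 from the success rates in section 1.1). That follows from the text and needs no simulation.

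The overfitting figures rest on assumptions that the article does not state: 7 to 11 candidates, all entered, no penalisation, no optimism correction, and markers that are noise. Under these, the mean apparent C-statistic is about 0.65 to 0.70 where the truth is 0.50. They show what could happen if the gap were filled carelessly, not what the investigators have said they will do.

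The point is separate from multiple testing: controlling the error rate over single markers would not correct the apparent accuracy of a combined panel.

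**What to change.** - **Section 2.13:** before outcomes are known, specify one multivariable model for one-year recurrence, with few terms or with penalisation. Name the markers that enter, including which atrial volume and which fat measure.
- **Section 2.13:** report the model's C-statistic and calibration slope after bootstrap optimism correction, repeating any selection step in every resample. The existing two-group tests can stay as description.
- **Abstract and sections 3 and 4:** limit the panel and independent-predictor claim to *develop and internally validate*, and leave external validation to another cohort.

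The cost is some added analysis, a less favourable reported C-statistic and a more modest claim. No new patients, visits or measurements are needed. If an unseen analysis plan already contains such a model, it is enough to bring 2.13 and the wording of the claims into line with it.

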## Conclusions

4

FIBRO-RISK will be the first CMR-based study that will investigate the impact of inflammation-mediated myocardial fibrosis on the risk of recurrence after successful catheter ablation of AF, aiming to validate inflammatory biomarkers and myocardial fibrosis as predictors for AF recurrence.
